## **C. Approach**

### **C.1 Overview and Design**

The primary purpose of this trial is to investigate whether true acupuncture is more effective than sham acupuncture or standard care for preventing radiation-induced xerostomia. Prior to radiation therapy, patients will be randomized into three groups: G1 (n=100) will receive true acupuncture, G2 (n=100) will receive sham acupuncture, and G3 (n=100) will receive standard care. Patients in the acupuncture treatment groups will receive up to 21 treatments over the course of radiotherapy with no more than 3 treatments per week. The duration of acupuncture therapy in the proposed study is the same as in our pilot trials. It has been shown to have a good effect in our phase II trial and small placebo controlled trial conducted at Fudan Cancer Hospital. Furthermore, inconvenience is minimized for participants because acupuncture is provided on the same day as radiation therapy.

Potential study participants will be identified by faculty in the departments of Radiation Oncology at Fudan Cancer Hospital and M. D. Anderson and referred to the research nurse for assessment of eligibility and informed consent counseling. Potentially eligible patients will be contacted in person when they are in the clinic so that the research nurse can describe the study in detail, answer the patients' questions, and assess their interest in the study. Approximately half the patients will be recruited from each center (193 patients at MD Anderson and 242 at Fudan) for a total sample size of 435 patients (see Appendix D. Study Schema, Study Schedule, Study Timeline).

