### **C.2 Eligibility and Participants**

**Inclusion criteria:** Adult  $\geq 18$  years of age and able to give informed consent; Diagnosed with head and neck cancer, which will be primarily oropharyngeal, and scheduled to undergo IMRT with or without concurrent chemotherapy at M. D. Anderson. Treatment plan that includes external beam radiation at a mean dose of at least 24 Gy or more to one of the parotid glands (the other gland can receive less than 24 Gy); Anatomically intact parotid and submandibular glands; Karnofsky performance status  $> 60$  (see Appendix E);

**Exclusion criteria:** History of xerostomia prior to head and neck radiation therapy or history of Sjögren's disease or another underlying systemic illness known to cause xerostomia; Prior head and neck radiation treatment; Suspected or confirmed physical closure of salivary gland ducts on either side; Known bleeding disorders or taking any dose of warfarin or heparin; Upper or lower extremity deformities that could interfere with accurate acupoint location or alter the energy pathway as defined by traditional acupuncture theory; Local skin infections at or near the acupuncture sites or active systemic infection; History of cerebrovascular accident or spinal cord injury since the mechanism of acupuncture may be associated with central nervous system activity; Mental incapacitation or significant emotional or psychiatric disorder that, in the opinion of the investigator, precludes study entry as these patients may not be able to cooperate with this slightly invasive procedure or with the data collection process; Current acknowledged use of any illicit drugs or evidence of alcohol abuse as defined by The American Psychiatric Association criteria (62); Current acknowledged use of other alternative medicines, such as herbal preparations, that could affect salivary function. If a patient is using any salivary substitute, they will be asked to refrain from using for at least 24 hours prior to saliva and questionnaire data collection. Each patient will be asked for a list of herbal supplements they are currently taking, and this will be reviewed on an individual basis.

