Patients will be excluded if they are taking any herbs known or suspected to affect salivary function. Participants taking amifostine, cholinergic agonist medications (pilocarpine, cevimeline), certain beta adrenergic antagonists, anticholinergic agents, saliva substitutes or other medications known to affect salivary function will also be excluded (see Appendix F). If a patient reports use of one of the prohibited medications, they will be considered non-compliant and dropped from the study. Finally, participants will be excluded who are currently receiving acupuncture for any condition or if they have ever used acupuncture before. If a participant is admitted to the hospital for any reason during the treatment period, an in-patient order for treatment will be requested.

**Participants:** Over 400 patients undergo IMRT radiation for head and neck cancer each year at M. D. Anderson or one of its satellite clinics. Within the next 2 years at least two more satellite clinics will open, increasing the possible patient base. At Fudan Cancer Hospital, approximately 450 patients undergo IMRT for NPC each year. Our pilot study experience at both institutions suggests that approximately 70% of these patients will be eligible for the proposed study. Therefore, at least 500 patients will be eligible per year for a total of over 1500 patients during the 36 months designated for recruitment.

All eligible patients will be asked to participate. We expect a relatively modest acceptance rate of approximately 60%. Patients generally decline either because they do not want to be randomized or because of time constraints. This conservatively estimated patient accrual rate would permit us to recruit at least 70 patients per year at each institution. In our previous studies, the attrition rate was less than 20%; however with longer follow-up, we expect the rate will increase somewhat. Thus, with even slightly higher attrition, we will still be able to accrue at least 50 evaluable patients per year per institution, for a total of 300 evaluable patients over the approximate 3 years of recruitment (n=100 per group; n=125 per group before attrition).

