At each acupuncture visit, vital signs (blood pressure, pulse) will be taken, and medications will be reviewed prior to the acupuncture treatment. Since the SC group does not receive acupuncture, they will not have vital signs taken and medications will not be reviewed on a weekly basis. All measures will be collected again during the course of radiation treatment (mid-treatment; except the assessment of salivary constituents), at the end of the radiation treatment period, and at 2-4, 5-9, and 10-15 months. These assessments may be collected over the phone if the patient is unable to come to MD Anderson. Patients will also be asked to complete a form about their oral hygiene. All patients will be provided with standard oral care recommendations. These include keeping their mouth clean by brushing their teeth at least two times a day and preferably after each meal. They will be also encouraged to not use candies, lozenges, or drink sugary beverages. They will also be told to consume up to 1.5 liters a day of water to help diminish the effects of radiation-induced xerostomia and keep hydrated.

Follow-up assessments will be obtained 2-4, 5-9, and 10-15 months after the end of radiation treatment for a total of 6 assessments (baseline; middle of radiotherapy; end of radiotherapy; and 2-4, 5-9, and 10-15 months after the end of radiation treatment). Participants will be given a small gift certificate (100 RMB [approximately \$15] value at Fudan Cancer Hospital; \$35 value at M. D. Anderson) for completing each assessment. After all data are collected at the 12-month follow-up visit, patients in the G2 and G3 study arms will be offered true acupuncture treatment for free for one week (3 treatments). For the complete study schema, schedule, and timeline please see Appendix D. All data collection will be conducted by research staff who are blinded to group assignments. A procedures manual will be developed that will include all aspects of conducting the trial, including the acupuncture treatments.

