Patients will be randomized by a form of adaptive randomization, called minimization, because simple randomization could result in covariate imbalances (63). Statistical adjustment of covariates can take imbalances into consideration, but results are generally more credible when they are obtained from groups with comparable baseline distributions. In minimization, group assignment is done sequentially. In this study, the patient characteristics used for group assignment will be stage of disease, age (running mean), sex, the mean planned parotid doses (left and right side will be calculated separately and balanced between groups; <10, 10-<20, 20-<26, 26-<30, 30-<35, 35-<40, 40-<50, 50-<60, ≥60), induction therapy (yes/no), and concurrent chemotherapy (yes/no). Randomization will be conducted at each site separately. This will ensure equal distribution of all factors across all groups and balanced at each site. Information on group assignment will be only communicated to the acupuncturists by the data managers to insure that the research staff remains blinded.

Treatment will be withheld if lab values are not within an acceptable range (ANC>500; platelet count>20K/ml; INR, 3.0); if the study participant is diagnosed with a mental incapacitation or significant emotional or psychiatric disorder that interferes with his/her ability to cooperate with study procedures; or if a participant receives any heparin or warfarin during the treatment period.

Participants will be dropped from the study, at any point during the study, if the participant begins taking a prohibited medication (Appendix F) or if the participant encounters a cerebrovascular accident or spinal cord injury.

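### Participants who begin a prohibited medication leave the study with no further XQ provided for, and medications are reviewed less often in standard care, so outcome-related missing data may differ between acupuncture and standard care

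*Supplement*

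**What the plan says.** All references are to the Final Protocol, whose section C.6 is the current analysis plan.

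- **Removal.** C.3: "Participants will be dropped from the study, at any point during the study, if the participant begins taking a prohibited medication (Appendix F". C.2 has a parallel rule triggered by patient report: "If a patient reports use of one of the prohibited medications, they will be considered non-compliant and dropped from the study".
- **What is prohibited.** Besides amifostine, pilocarpine and cevimeline, C.2 lists "certain beta adrenergic antagonists, anticholinergic agents, saliva substitutes or other medications known to affect salivary function will also be excluded". The full list is in Appendix F, which is not among the pages available.
- **Saliva substitutes.** C.2 also says: "If a patient is using any salivary substitute, they will be asked to refrain from using for at least 24 hours" before each data collection. That reads as tolerated use, and it sits beside the exclusion of users.
- **Review of medications.** C.3 says that at each acupuncture visit "medications will be reviewed prior to the acupuncture treatment". C.1 allows "up to 21 treatments over the course of radiotherapy with no more than 3 treatments per week", and C.4.b puts sham on the same schedule as true acupuncture. For standard care, C.3 says "they will not have vital signs taken and medications will not be reviewed on a weekly basis".
- **Analysis.** C.6.a compares the three arms at the end of radiotherapy by analysis of variance, and fits a mixed model to post-intervention XQ with baseline as covariate. C.6.b keeps early drop-outs in the mixed model. It claims unbiasedness if missingness depends only on covariates in the model, and offers multiple imputation if the data appear not to be missing at random. It also describes complete-case analyses and labels them intent to treat.

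**The concern.** Several prohibited products are treatments for dry mouth, and section A itself names pilocarpine and saliva substitutes as such. A patient whose mouth becomes dry enough to need one is plausibly a patient with a high XQ. Ending that patient's participation makes later XQ values missing for a reason tied to the outcome.

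A removal rule acts only on use that is found. In the acupuncture arms there are up to 21 occasions during radiotherapy to find it; in standard care there are fewer. The period of unequal review ends at the time point on which the trial was sized. At stake is whether the retained patients in the acupuncture and standard-care arms are still comparable as randomised. That is one of the two comparisons in the primary aim.

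**Working it through.** **1. The plan's own figures.** C.6.c: 0.4 SD, two-sided 0.05, 80% power. n per arm = 2 × (1.96 + 0.8416)² / 0.4² = 98.1, so 99; the plan uses 100, which gives power of about 81%. Total: 300 / (1 − 0.31) = 434.8, so 435. Both reproduce. The standard error of a difference at 100 per arm is √(2/100) = 0.1414 SD.

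**2. What the documents do not give.** There is no rate of prohibited-medication use, no share of the 31% attrition due to this rule, and no detection rate by arm. Everything below rests on assumptions.

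**3. Outright removal, no true effect.** Let z be standardised XQ at the end of radiotherapy. Assume P(use | z) = logistic(logit(b) + s·z), with s = 1.0 or 1.5 (odds ×2.7 or ×4.5 per SD), and a detected fraction d. The mean of those retained is E[z(1 − d·P)] / E[1 − d·P]. Bias is this mean at d = 1 (acupuncture) minus its value at the standard-care d. Negative values favour acupuncture.

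| b | s | use | d = 0.25 | d = 0.50 | d = 0.75 | d = 1 |
|---|---|---|---|---|---|---|
| 0.02 | 1.0 | 3% | −0.02 | −0.02 | −0.01 | 0 |
| 0.05 | 1.5 | 10% | −0.09 | −0.06 | −0.03 | 0 |
| 0.10 | 1.0 | 13% | −0.09 | −0.06 | −0.03 | 0 |
| 0.30 | 1.5 | 35% | −0.31 | −0.23 | −0.13 | 0 |

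The range is therefore about 0.01-0.10 SD at 3-10% use and 0.03-0.31 SD at 13-35% use.

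**4. Effect on the test.** Two-sided rejection is Φ(B/0.1414 − 1.96) + Φ(−B/0.1414 − 1.96), where B is the size of the bias. B = 0.03 gives 5.5%, 0.10 gives 11%, 0.15 gives 19% and 0.31 gives 59%.

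**5. Equal detection, true effect 0.4 SD.** This is the relevant case for true versus sham. The comparator arm has more users and loses more of its high scores. The same model loses 0.01-0.09 SD over the whole range of use. With SD held at 1 and 100 per arm, power falls from about 81% to Φ(0.39/0.1414 − 1.96) = 79% at best and Φ(0.31/0.1414 − 1.96) = 59% at worst.

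**6. Does a mixed model repair it?** A second model removes a top fraction q = 5-20% on a latent propensity correlated 0.5-1 with XQ, with half detection in standard care. Complete-case bias is about 0.03-0.19 SD. A missing-at-random analysis that also uses mid-radiotherapy XQ (assumed correlation 0.6, observed for everyone) reduces it to about 0.02-0.15 SD. The bias becomes smaller but does not disappear. A patient dropped before mid-treatment has no post-baseline XQ at all, and the analysis of variance has no value for anyone dropped before the end of radiotherapy.

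**The case against.** A reader might infer that the plan removes the patients with the worst XQ unequally by arm and so is biased towards acupuncture. The documents do not support that as stated.

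- **It is an inference.** The list also covers amifostine, certain beta adrenergic antagonists and anticholinergics, which are not dry-mouth treatments. If the 24-hour pause governs saliva substitutes, their use triggers no drop and the mechanism shrinks. This stands.
- **Less often is not never.** Standard-care medications are not reviewed weekly, but concomitant medications are taken at baseline, and C.3 repeats all measures at mid-treatment and at the end of radiotherapy. It is unclear whether that includes medications. A patient in any arm may also report use. Detection close to equal is possible, and the bias then approaches zero. This stands.
- **Use may be low.** Section A says pilocarpine is not commonly used in China, and C.1 assigns 242 of 435 patients to Fudan. The top of the 13-35% range exceeds the whole 31% drop-out allowance. The low rows of the table deserve equal weight.
- **Direction.** Undetected users kept in standard care may have their XQ lowered by the medication. That works against acupuncture, and the calculation sets it to zero. This stands.
- **Scope.** Unequal review does not touch true versus sham, and it is confined to radiotherapy. This stands.
- **C.6.b retains drop-outs.** The mixed model keeps XQ recorded before the drop, so these patients are censored rather than deleted. This stands in part: the stated condition for unbiasedness is doubtful when current dryness drives missingness, the imputation depends on a judgement that observed data cannot settle, and the complete-case wording points the other way.

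**Conclusion.** The concern holds in a limited form, and the plan should be changed. As written, it ends participation on an event plausibly related to XQ, provides for no XQ afterwards, and looks for that event on different schedules in the acupuncture and standard-care arms up to the end of radiotherapy. The planned analyses do not reliably cure this.

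The size is illustrative. With outright removal and standard-care detection at 25-75% of that in the acupuncture arms, the bias is 0.01-0.10 SD at 3-10% use and 0.03-0.31 SD at 13-35% use, against 0.4 SD in the design; it is zero with equal detection. For true versus sham, the cost is a likely dilution of about 0.01-0.09 SD if the true effect is 0.4 SD.

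Two stronger conclusions are not supported: that the result must favour acupuncture, and that the sham-controlled comparison suffers from unequal review. The net direction against standard care is unknown, and the sham schedule matches the true one.

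**What to change.** 1. State that a participant who begins a prohibited medication remains in all scheduled XQ and saliva assessments and is analysed in the randomised arm.
2. Record medications with the same form at the same six assessments in all three arms, and use only that record in any analysis definition. Reviews at acupuncture visits can continue for other purposes.
3. Pre-specify one sensitivity analysis that multiply imputes XQ after first prohibited-medication use, including a scenario not missing at random that differs by arm.
4. Reconcile the two statements on saliva substitutes in C.2, and the drop rule in C.2 and C.3 with the intent-to-treat and complete-case wording in C.6.b.

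None of this says which medications are allowed or whether acupuncture continues; those remain with the investigators.

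The cost is a protocol amendment and one medication form at visits that already take place. The downside is some dilution of the treatment contrast from medication use, which the sensitivity analysis would show. XQ that was not collected cannot be recovered later, so the change is worth most when made early.

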#### **C.4 Acupuncture Treatment Procedures**

Treatments will be given in the acupuncture clinics at M. D. Anderson and Fudan Cancer Hospital. Patients will be placed in a supine position and, thus, blocked from seeing any of the needles. The needles will remain in place for 20 minutes with each treatment. Standardized techniques for point location will be utilized, which are based on anatomical landmarks as well as proportional measurements using the patient's own body. For example, finger breadth is based on each patient's middle finger, and the proportional unit of measure, the "cun," is defined as the distance between the two medial ends of the creases of the interphalangeal joints when the middle finger is flexed (30, 64). The acupuncture procedures will be performed using standard aseptic technique (64). The needles come in individual sterile packages, and the same level of sterility as that used for an invasive medical procedure will be applied.

All treatment providers will be licensed, experienced acupuncturists. The acupuncturist and research nurses at Fudan Cancer Hospital have been trained at M. D. Anderson. Any new acupuncturists will have one-on-one training with the lead research acupuncturist from M. D. Anderson ([name]). All acupuncturists will also participate in a video-based training program. At the end of the training period, a return demonstration of 10 treatments (5 active and 5 sham) on individuals who are not potential study subjects will be required. Finally, in order to ensure continued quality control, participating acupuncturists will be observed and evaluated three times per year. Faculty and staff from M. D. Anderson will also visit Fudan Cancer Hospital twice a year to check on the running of the trial. We are confident in the quality control procedures in place as we have been conducting collaborative research now for over 6 years, including the specifics of this protocol in two different trials at Fudan Cancer Hospital.

##### **a. True acupuncture**

Although many point combinations could be used, the investigators have attempted to identify a set of acupuncture points that integrates TCM and biomedicine, with a focus on using a minimal number of sites. The active acupuncture points for this study were selected on the basis of successful experience from our pilot studies as well as on previously published trials (35-41, 45, 46, 65-67). Points were also selected on the basis of their indications according to the classical theory of TCM (30, 64) and current understanding of the various anatomical locations and neurovascular tissues associated with each point (68).

The body acupuncture points selected for this protocol are Ren 24, Lung 7 (LU 7), and Kidney 6 (K6). One placebo needle will also be placed at Gallbladder 32 (Gb32) on the right side. This is intended to provide participants in the active treatment group with a stimulus that will not elicit De Qi sensation. Ear points selected are Shenmen, Point Zero, Salivary Gland 2' (SG 2-prime), and Larynx. Except for Ren 24, which is located in the midline and the placebo needle at Gb32, all points will be treated bilaterally. The only facial point used in this study will be Ren 24. After careful consideration and discussion, we have chosen not to use points on the face that were selected in some prior studies (i.e., Stomach 4-7). Even though problems are rare, we prefer to err on the side of precaution and avoid needling tissues that may still be friable or easily injured after radiation. Furthermore, Johnstone et al. (35, 45, 46) obtained good results without using facial points. Ren 24 is located in the midline and should not pose a problem. Patients will be excluded from the study, however, if there is any indication of skin irritation or infection at this location.

Needle insertion endpoints will be the standardized recommended depth of insertion (30, 64) or achievement of De Qi sensation per the acupuncturists' determination. De Qi is a feeling of

tingling, aching, numbness, or warmth at the acupuncture site. Acupuncturists also describe this feeling as if the muscle is grabbing the needle. Propagation of this sensation along acupuncture channels is thought to carry the therapeutic signal to target areas (30, 68). Once the standard depth of insertion or De Qi is achieved at the body points, the needles will not be manipulated further unless one becomes displaced. No electrical stimulation will be applied to the needles in this study. Acupuncture needles used for the body points will be 0.25 x 40-mm in length and for the ears 0.16 x 15-mm in length (see Appendix G for further details).

#### **b. Sham acupuncture**

Well-designed clinical acupuncture trials require a sham procedure that is indistinguishable from the real treatment, yet inactive. Although no “gold standard” has been established for placebo controls in acupuncture trials, ideally, non-penetrating needles placed at inactive points should be used. Park and colleagues validated a non-penetrating, telescoping needle with a separate device that attaches it to the skin (69, 70). This device will be used on body points in the proposed study but is too heavy and bulky for use on auricular points. For sham auricular points, Usichenko and colleagues have used points on the helix of the ear with success in 3 different studies (71-73). We propose to use a similar procedure for this study.

The sham procedure for participants in G2 is: Sham Location 1 - placebo needle at inactive point located 0.5 cun below and 0.5 cun lateral to CV 24 on the chin (for participants who have beards this point may be omitted and indicated on treatment forms); Sham Location 2 - placebo needle at inactive point located 0.5 cun radial and 0.5 cun proximal to SJ 6 between SJ and LI Channels (bilateral upper extremities); Sham Location 3 - placebo needle at inactive point located 1.0 cun below and 0.5 cun lateral to St 36, between St and Gb Channels (bilateral lower extremities). In order to elicit De Qi in the control group, one 0.25 x 40mm acupuncture needle will be used at Gb 32 above the right knee. This point is not indicated for dry mouth. Finally, four 0.16 x 15mm acupuncture needles on the helix of each ear (8 ear points) will be included. Location of inactive points will be confirmed with an electrodermal point finder.

The sham treatment will be given according to the same schedule as the true acupuncture treatment. Participants in both groups will be placed in a comfortable position. Each point will be identified and marked on the skin. A total of 14 points will be used in both groups. As the active acupuncture group is receiving treatment using a placebo needle and the placebo acupuncture group is receiving active treatment at a real acupuncture point (both at Gb 32) and with acupuncture needles inserted at inactive points on the ear, the blinding of the two groups should be excellent. In the two-arm placebo-controlled pilot study conducted at Fudan Cancer Hospital using the same two acupuncture groups (G1 and G2), perfect blinding was indicated (see C.9 below).

